##### EXCLUSION CRITERIA

- Fetal malformations
- Symptomatic uterine contractions
- Contraindication for vaginal delivery
- Medical indication of induction of labor or elective cesarean delivery
- Maternal desire to induce labor
- Maternal negative to enrollment
- Language barrier
- Inability to give consent

Specific Exclusion Criteria for Pregnotia System (if any of these criteria is present, the measurement of cervical stiffness using Pregnotia aspiration device will not be performed):

- Müllerian anomalies with two cervixes
- Severe vaginal bleeding
- Cervical dilatation
- Known HIV
- Visible, symptomatic cervical or vaginal infections
- If one of the following conditions is present on the cervix at the 12 o'clock position:
  - o Nabothian cyst
  - o Cervical myomas
  - o Cervical condylomas
  - o Squamous intraepithelial lesion
  - o Conization/LEEP2/LLETZ3
  - o Cervical endometriosis
  - o Cervical tears
  - o Cervical dysplasia
  - o Large ectopy, for which it is not possible to find a suitable location near the ectopy where native tissue is present
  - o Large scar tissue, for which it is not possible to find a suitable location near the scar where native tissue is present.

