## 4 STATISTICS AND METHODOLOGY

### 4.1. Statistical analysis plan

#### MAIN ANALYSIS

The main outcome (spontaneous onset of labor vs. induction of labor between 41 and 42 weeks of pregnancy due to gestational age) will define two groups. The distribution of continuous or categorical variables among the units will be compared using Student's T test or Fischer's exact test, respectively. Two-sided significance level was set to 0.05.

A model of prediction of the binary outcome will be elaborated using stepwise backward and forward logistic regression analysis, including all analyzed features (gestational age at data collection will be included as an independent variable). To add or remove variables from the model, p-values of 0.05 or 0.10 will be used, respectively. Goodness-of-fit of the model will be evaluated using Hosmer and Lemeshow test and, if multiple models are achieved, the best one will be selected searching parsimony and following Akaike's Information Criterion. Area under the Receiver-Operating Characteristics curve will be used to assess predictive ability of the model. This value will be also calculated using bootstrapping resampling methods (1000 repetitions) to internally validate the results. As only a subset of the sample will have the measurement of cervical stiffness using Pregnotia device (as this assessment was lately introduced), a secondary analysis (following the same principles of the main analysis) will be performed. A correlation analysis will be carried out comparing cervical consistency index evaluated by ultrasound with cervical stiffness assessed using the aspiration device, as both measurement evaluate the same biophysical characteristic of the cervix.

The probability of spontaneous onset of labor for each day after the analysis will be evaluated using survival regression models. The data will be described using Kaplan-Meier's non-parametrical survival function and the predictive model will be estimated using stepwise backward and forward Cox's regression (proportional hazards model). As mentioned before, data regarding women whose labors have been induced due to maternal or fetal indication (different from gestational age) or with prelabor rupture of membrane without spontaneous onset of labor after 12 hours of expectant management will be censored at the time of admission for these causes.

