## 8 FUNDING / PUBLICATION / DECLARATION OF INTEREST

The developers of fetal Fibronectin determination kits (Hologic®) will provide them, along with the analyzers at no cost for the researchers. Funding and supplies support will be asked to the developers of Placental alpha macroglobulin 1 determination kits (Qiaogen®).

Regarding the collaboration with the enterprise “Pregnotia AG®”, which will be providing the device for the measurement of cervical stiffness, a collaboration contract has been established. One Pregnotia Control Unit , as well as 240 disposable Pregnotia Probes, will be provided free of charge for the conduct of the research.

Both enterprises have been informed that the study protocol will be published, as well as the conclusions of the research, whatever are the results. The design of the study, the data collection, analysis and publication are an exclusive responsibility of the researchers and no interference from the enterprises is expected. Data will not be shared, and the companies will only know the results once the analysis has finished.

The researchers are workers paid by the institutions involved in the study and will not receive any compensation for participating in the study. Once collaboration contracts are established with any of these two companies, SwissEthics will be immediately informed.

The contract regarding multicentric collaboration is attached to this protocol.

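### The stiffness analysis reruns the stepwise search in a differently composed subset, so the plan does not directly estimate what stiffness adds to prediction

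*Protocol*

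**What the plan says.** Section 2.2 lists the stiffness index among the predictors. Section 4.1 (Main analysis) then separates it from the main model, with late introduction of the device as the reason: "As only a subset of the sample will have the measurement of cervical stiffness". For those women, "a secondary analysis (following the same principles of the main analysis) will be performed".

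The principles referred to stand in the same paragraph: "stepwise backward and forward logistic regression analysis, including all analyzed features", with these thresholds: "To add or remove variables from the model, p-values of 0.05 or 0.10 will be used, respectively". Model choice by Akaike's criterion, the AUC, and a bootstrap of the AUC with 1000 repetitions follow.

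The only direct use of stiffness beside another measure is this: "A correlation analysis will be carried out comparing cervical consistency index evaluated by ultrasound with cervical stiffness assessed using the aspiration device".

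Section 3.1 gives device-specific exclusions, among them cervical dilatation (no threshold stated) and a list of local cervical findings. If one is present, "the measurement of cervical stiffness using Pregnotia aspiration device will not be performed"; the woman remains in the study. Section 3.3 adds that a reading counts only if the first of three measurements succeeds. Section 4.2 drops women with a missing predictor from the regression models. Section 8 records one control unit and "240 disposable Pregnotia Probes" supplied free of charge. No section states how many women will have a reading.

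**The concern.** For a late-arriving predictor, the useful question is whether it improves prediction beyond the features already in the model. The plan builds two models that differ in more than stiffness:

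- **Sample.** The stiffness model uses only women with a reading, who are later recruits. Centre mix may differ too, since the multicentre phase also began late.
- **Case mix.** Dilated women are in the main model but cannot be in the stiffness model. Dilatation is a cervical state close to what the Bishop score records and plausibly close to the outcome.
- **Selected predictors.** The search is rerun, so the other variables in the stiffness model need not be those of the main model.

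A reader will naturally set the two AUCs beside each other. Their difference would mix the contribution of stiffness with these other sources, and it could point either way when stiffness contributes nothing.

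**Working it through.** **Inputs.** 78% spontaneous onset, 22% other, 10 events per variable, 15 variables, two models and 10% missing predictors (section 3.1, Sample size); 240 probes (section 8); 60% undelivered at the second visit (section 3.3).

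**1. The plan's own figure.** 10 / 0.78 = 12.8, rounded up to 13 women per variable. 13 × 15 × 2 = 390, and 390 × 1.10 = 429. The stated figure reproduces. One model of 15 variables therefore needs 13 × 15 = 195 women under the plan's rule.

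**2. Size of the stiffness subset.** If each probe serves a different woman, 240 / 429 = 56% of the cohort is the ceiling. With 10% missing predictors, 240 × 0.90 = 216, which exceeds 195. If, as an assumption, 60% of measured women also used a probe at 40 weeks, the supply would cover 240 / 1.6 = 150 women, or 150 × 0.90 = 135 complete cases, below 195.

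**3. Smaller outcome class per candidate.** With a share p in the smaller class, 240 women give 240p / 15 = 16p per candidate.

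- p = 0.22 as a pure proxy: 240 × 0.22 = 53 women, 3.5 per candidate. For 216 complete cases: 47.5 women, 3.2 per candidate.
- The same proxy at 150 women: 33 women, 2.2 per candidate.
- The largest possible value, p = 0.5: 120 / 15 = 8, still under 10.

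The proxy has a known weakness. Section 3.1 describes the 22% as inductions for reasons other than gestational age, whereas the comparison group in section 2.2 is induction because of gestational age. The share of that group is not given and could be lower.

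**4. What a rerun search does.** This simulation rests on assumed effects: 15 candidates, five real predictors besides stiffness, stiffness correlated with three other cervical predictors, about 22% non-spontaneous, and backward removal at 0.10. The percentages are the runs in which stiffness was kept.

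| Women in the model | No stiffness effect | Log odds ratio 0.3 per SD | Log odds ratio 0.5 per SD |
|---|---|---|---|
| 386 (429 × 0.90) | 9% | 66% | 96% |
| 216 | 12% | 48% | 85% |
| 135 | 14% | 38% | 70% |

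Retention thus carries some information, but at 216 women a modest real effect is kept in only about half the runs. When the main search used 386 women and the subset search used 216 of them, the other predictors chosen were identical in only 9% of runs.

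**5. What case mix alone does.** One fixed model without stiffness had an AUC of 0.751 in the full simulated population. Removing the top 10% to 40% on one cervical predictor, as a stand-in for dilatation, lowered it to between 0.738 and 0.719, a drop of 0.013 to 0.032. The documents give no share of dilated women, so this shows a direction and a possible order of size only.

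**The case against.** The best defence is that no stated objective is the increment of stiffness over the main model, and section 4.1 plans no contrast between the two AUCs. Reporting such an increment could be left to a statistical analysis plan. This is partly right: the misleading comparison is one that readers would make, not one that the protocol announces. But the protocol does fix the method for the subset, and that method does not give the quantity of interest for a predictor it lists.

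Several stronger readings are tempting and are not supported:

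- **That the analysis can show nothing about stiffness.** If stiffness is kept, its coefficient is adjusted for the other selected predictors. That is evidence, though weakened by selection and confined to measurable women.
- **That the subset is small.** No size is stated, and a subset of 240 would pass the plan's own 195 per model. It looks thin only when the smaller class is counted.
- **That overfitting is ignored.** The bootstrap of the AUC carries over to the subset. It addresses optimism; it does not remove the difference in women or case mix.
- **That the 22% is the comparison class, or that only 150 women can be measured.** The first is a proxy. The second assumes a repeat reading at 40 weeks, which no section states, and Appendix 1 shows a single assessment visit.

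It also stands that the case-mix effect in the simulation is modest, 0.013 to 0.032 in AUC under assumed removals.

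**Conclusion.** The point holds in a limited form. The plan reruns the whole search in women who differ from the main cohort in recruitment period and cervical state, and nowhere compares prediction with and without stiffness in the same women. It therefore does not directly estimate what stiffness adds. The finding rests on the text of sections 3.1 and 4.1 and does not depend on the simulation or on the 22%. The figures show scale only: at most 56% of the planned cohort measured, and about 3.5 women in the smaller class per candidate under the proxy, fewer if probes are also used at 40 weeks. Severity is minor to moderate, because one secondary analysis is affected and the main model is untouched.

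**What to change.** Reword the stiffness paragraph of section 4.1, or settle it in the statistical analysis plan before analysis:

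1. In women with a valid reading, refit the predictors selected in the main model, once without and once with stiffness as a single added term. Test that term by a likelihood-ratio test on one degree of freedom.
2. Report the optimism-corrected change in AUC in those same women as the main stiffness result, with both models fitted in the same bootstrap resamples.
3. Refit the coefficients; do not carry the main model's score forward unchanged. Section 4.1 holds that the ultrasound consistency index measures the same characteristic, so its weight must be free to move when stiffness enters.
4. Label any new stepwise search in the subset exploratory, and do not set its AUC against the full-cohort AUC.
5. State the expected number of measured women and of gestational-age inductions among them. Tabulate measured against unmeasured women by reason (before introduction of the device, device-specific exclusion, invalid reading) and by outcome.
6. Limit the conclusion to women eligible for the measurement.

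The cost is wording and slightly more analysis, with no new data. The price in method is that the other predictors are not reselected around stiffness in the main stiffness result.

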#### *Secondary objectives*

1. To analyze the individual accuracy of each of the evaluated characteristics at 385/7-39 weeks of pregnancy to diagnose the onset of spontaneous labor.
2. To establish the influence of each variable and the predictive models in the daily probability of spontaneous onset of labor after 385/7-39 weeks of pregnancy.
3. To analyze the individual accuracy of each of the evaluated characteristics at 39 and 40 weeks of pregnancy to diagnose the onset of spontaneous labor within 1 or 2 weeks.
4. To evaluate the performance, at 39 and 40 weeks of pregnancy, of different features in predictive models, designed to evaluate the probability of spontaneous onset of labor within 1 or 2 weeks.
5. To establish the influence of each variable and the predictive models in the daily probability of spontaneous onset of labor within 1 or 2 weeks after 39 and 40 weeks of pregnancy.

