#### SECONDARY ANALYSIS (STRATIFICATION BY GESTATIONAL AGE)

Besides the analysis that guides the design of the study, both logistic regression and survival analysis will be performed as follows:

- (1) For data collected at  $38^{5/7}$ - $39^{6/7}$  weeks of gestation: Probability of outcome in 7 and 14 days after data collection.
- (2) For data collected at 40 weeks ( $40^{0/7}$ - $40^{6/7}$ ) of gestation: Probability of outcome in 7 and 10 days after data collection.

The same censorship criteria will be applied.

All statistical analysis will be performed using Stata 16.1 software (StataCorp, Texas, USA).

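### Secondary objectives 2 and 5 ask for the influence of each variable on the daily probability of labour, but the only time-to-event regression named is a stepwise Cox model, which gives no estimate for the variables it drops

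*Protocol*

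**What the plan says.** Section 2.1 of the protocol sets secondary objective 2 as "To establish the influence of each variable and the predictive models in the daily probability of spontaneous onset of labor after" the first examination. Secondary objective 5 repeats the aim "in the daily probability of spontaneous onset of labor within 1 or 2 weeks after 39 and 40 weeks of pregnancy". Both name two targets: each variable, and the predictive models.

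Section 4.1, Main analysis, opens the survival part with "The probability of spontaneous onset of labor for each day after the analysis will be evaluated using survival regression models". It then names a Kaplan-Meier description and one regression: "the predictive model will be estimated using stepwise backward and forward Cox's regression (proportional hazards model". Selection thresholds appear earlier, in the logistic paragraph: "To add or remove variables from the model, p-values of 0.05 or 0.10 will be used, respectively". They are not restated for Cox.

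The only comparison made variable by variable in section 4.1 is between the two groups of the binary outcome: "The distribution of continuous or categorical variables among the units will be compared using Student's T test or Fischer's exact test, respectively". The analysis stratified by gestational age says that "both logistic regression and survival analysis will be performed as follows" and adds no per-variable model.

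Three further statements bear on the remedy:
- Section 4.1 says that cervical stiffness was introduced late, exists for only part of the sample and gets its own secondary analysis.
- Section 4.2 removes from the regression models any participant with a missing predictor.
- Section 8 lists 240 disposable probes for the stiffness device.

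**The concern.** A stepwise Cox model can serve the half of objectives 2 and 5 that concerns the predictive models. It cannot serve the half that concerns each variable. A removed variable leaves no hazard ratio and no interval, so there is no bound on the effect that may have been missed. Retained variables do have estimates, but these tend to be too large. They were kept because they looked strong, and they also absorb part of the effect of correlated variables that were dropped.

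Correlation is plausible here. The endpoint table in section 2.2 lists Bishop score, cervical length, head-to-os distance, posterior cervical angle, consistency index and stiffness, all of which describe the same cervix. Section 4.1 itself says that the last two measure the same property. At stake is whether the study can say, for each marker, how much it shifts the daily chance of labour and how precisely that is known.

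**Working it through.** **1. The plan's own figure.** Inputs from section 3.1, Sample size: 78% spontaneous onset, 10 events per variable, 15 variables, two models, 10% for missing predictors.
- 10 / 0.78 = 12.8, rounded up to 13 women per variable.
- 13 x 15 x 2 = 390, and 390 x 1.10 = 429.

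Both stated numbers reproduce. Expected events among complete cases: 0.78 x 390 = 304.

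**2. Chance that a real predictor misses the threshold.** The protocol gives no effect sizes or correlations, so these are assumed: HR per SD from 1.10 to 1.30, and R2 with the other predictors of 0 or 0.5. With m = sqrt(events x (1 - R2)) x ln(HR), the chance of passing is Phi(m - z) + Phi(-m - z), where z = 1.645 for p < 0.10 and 1.960 for p < 0.05.

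Example, HR 1.15 and R2 = 0: m = sqrt(304) x ln(1.15) = 17.44 x 0.1398 = 2.44. Phi(2.44 - 1.645) = 0.79, so the predictor misses in 21% of cases.

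| HR per SD | Misses p<0.10, R2 0 / 0.5 | Misses p<0.05, R2 0 / 0.5 |
|---|---|---|
| 1.10 | 49% / 68% | 62% / 78% |
| 1.15 | 21% / 47% | 32% / 59% |
| 1.20 | 6% / 27% | 11% / 39% |
| 1.30 | 0% / 6% | 0% / 10% |

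**3. Check by simulation.** Stepwise Cox, n = 390, about 80% events, 15 predictors, entry at 0.05 and removal at 0.10, 150 runs per HR. Eight predictors had a real effect; five of these were correlated at 0.5 and three were independent.

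| True HR | Dropped: independent / correlated | Mean HR when kept: independent / correlated | Full model mean HR: independent / correlated |
|---|---|---|---|
| 1.15 | 24% / 33% | 1.18 / 1.23 | 1.15 / 1.16 |
| 1.20 | 7% / 19% | 1.21 / 1.25 | 1.21 / 1.20 |
| 1.30 | 0% / 3% | 1.31 / 1.32 | 1.31 / 1.31 |

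Null predictors stayed in 9-13% of the time. The unselected model recovered the true values closely.

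**4. The 40-week data.** Section 3.3 expects 257 women at the second visit. If 78% had events (an assumption), that is about 200. The same formula at p < 0.10 gives misses of 37-60% at HR 1.15 and 18-43% at HR 1.20. Women first approached at 40 weeks would reduce these figures somewhat.

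**5. Room for an unselected model.** 304 / 15 is about 20 events per variable; without stiffness, 304 / 14 is about 22. If stiffness is included, the complete-case rule limits the model to women who have it. If each of the 240 probes serves one woman (an assumption), that is at most 240 women and 0.78 x 240 = 187 events, or 187 / 15, about 12 per variable.

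**The case against.** The strongest reply is that the protocol ties stepwise selection only to the predictive model, while the sentence before it speaks of survival regression models in the plural. Per-variable Cox models could fall under that wording, and which hazard ratios to tabulate is often left to a separate SAP, which is not at hand. This reading is possible. But section 4.1 fixes the method, names no other regression and gives no rule for reporting dropped variables. Naming the per-variable models is therefore a real change to the plan.

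A second reply is that every feature is reported elsewhere, through the group comparisons and the individual-accuracy objectives (secondary objectives 1 and 3). That is true, and a marker dropped from Cox may still show an association there. But the group comparisons have no time scale and no censoring, and neither analysis gives an effect on the daily probability.

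A reader might go further and infer that dropped markers will be declared unhelpful, that which cervical measure survives is largely chance, or that the miss rate is high whatever the true effect. The documents do not support this. Nowhere do they say that a dropped variable will be reported as having no influence. They give no correlations or effect sizes, and at HR 1.30 the loss is small. Stiffness is also outside the main model, so that model holds five of the six cervical measures.

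**Conclusion.** The point holds as a mismatch between objective and method. As written, the plan leaves each variable that stepwise Cox removes without a hazard ratio or interval, although objectives 2 and 5 ask about each variable. That gap exists at any effect size.

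How often it would affect a real predictor depends on assumptions. With 304 events and removal at p = 0.10, it is about 21-47% at HR 1.15 per SD and 6-27% at HR 1.20, for R2 from 0 to 0.5. It falls to 0-6% at HR 1.30. Applying the logistic thresholds to Cox is itself an assumption. Inflation of retained estimates was modest for independent predictors (1.18 for a true 1.15) and larger for correlated ones (1.23).

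Only secondary objectives are affected. The primary objective concerns the performance of predictive models, and this point does not bear on it. The change is worth making because it is cheap and no other named analysis fills the gap.

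**What to change.** In section 4.1, for objectives 2 and 5 and within each gestational-age stratum, report for every listed predictor the hazard ratio (per SD or per category) with 95% CI from:

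- (a) a Cox model that accounts for gestational age at data collection, using all women who have that predictor;
- (b) a full Cox model without selection, containing all predictors except cervical stiffness.

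Estimate stiffness, and any full model that includes it, only in the measured subset and as a separate analysis, as section 4.1 already plans. Putting stiffness into model (b) would, under the complete-case rule in section 4.2, discard the data on the other 14 predictors for every woman without a probe measurement.

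Keep the stepwise model as the prediction tool. State the selection thresholds that apply to it, and state that omission from it is not evidence of no influence.

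The cost is one extra table and a few sentences, with no new data collection. Intervals will be wide for the correlated cervical measures, for stiffness and for the smaller 40-week data set; that width reflects what the study can actually tell about them.

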## 2.2 Primary and secondary endpoints

| VARIABLE TYPE                                      |  | VARIABLE AND SOURCE OF INFORMATION                                                                                                                                                                 |                       |
|----------------------------------------------------|--|----------------------------------------------------------------------------------------------------------------------------------------------------------------------------------------------------|-----------------------|
| Main outcome (1)
(logistic regression analysis) |  | Spontaneous onset of labor between 39 and 41 3/7 weeks of pregnancy
vs.
Induction of labor between 41 3/7 and 42 weeks of pregnancy due to gestational age             |                       |
|                                                    |  | Gestational age at spontaneous onset of labor (days after last menstrual period)                                                                                                                   |                       |
| Main outcome (2)
(survival analysis)            |  | Gestational age at spontaneous onset of labor (days after last menstrual period)                                                                                                                   |                       |
| Censorship                                         |  | Induction of labor due to maternal or fetal indication, different from gestational age.
Prelabor rupture of membrane without spontaneous onset of labor after 12 hours of expectant management. |                       |
| Predictors                                         |  |                                                                                                                                                                                                    |                       |
| Clinical                                           |  | Maternal age (years)
Maternal height (cm)
Closest to admission maternal weight (kg)
Previous vaginal deliveries
Previous cesarean deliveries
Expected delivery date                 |                       |

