### SAMPLE SIZE

According to our data, approximately 78% of women will start their labor spontaneously before 41 weeks, meaning that 22% will have an induction of labor for medical reasons other than gestational age. Hence, considering 10 events (spontaneous onset of labor) for each of these 15 variables, and doubling this quantity for the elaboration of two different models, 13 participants will be required for each of these variables, hence 390 women are needed. Assuming a 10% rate of women with missing values in at least one predictor, 429 **patients** are needed.

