### **3.4 Withdrawal and discontinuation**

Women may abandon the study at any time upon request, if they decide to withdraw their informed consent. In this case, they will be asked to decide about the destination of the information that has already been collected.

- If she decides not to consent any use of their data, the corresponding entrance will be removed from the database and all the paper documentation regarding their participation will be destroyed, complying with legal requirements.
- If she decides to consent the utilization of data, it will be kept as the rest of the data and the follow-up will be censored at the time of consent withdrawal.

It may also be possible that women discontinue their participation if a medical indication for elective cesarean delivery or induction of labor (different from gestational age) arises during the follow-up. In this case, censorship will be established at this point.

If perinatal outcomes are missing (due to delivery in another center, for example), follow-up will be considered up to the last medical registry and censored afterwards.

This potential loose of information has been considered in the design and the sample size has been adequately adjusted.

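### The 12-hour rule for prelabour rupture of membranes records some spontaneous labours as censored, and its censoring date can be read as depending on later events; the numerical effect is small

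*Protocol*

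**What the plan says.** Protocol section 2.2 defines main outcome (2), for the survival analysis, as "Gestational age at spontaneous onset of labor (days after last menstrual period"). It sets no limit on the time since membrane rupture. The censorship row of the same table lists "Prelabor rupture of membrane without spontaneous onset of labor after 12 hours of expectant management" and gives no date for the censoring.

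Section 4.1 (Main analysis) supplies the date. Women induced for a maternal or fetal indication other than gestational age, and women with prelabour rupture "without spontaneous onset of labor after 12 hours of expectant management will be censored at the time of admission for these causes". The model is meant to give "The probability of spontaneous onset of labor for each day after the analysis".

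Section 3.4 deals with an indication for induction or elective caesarean that arises during follow-up: "In this case, censorship will be established at this point". The secondary analysis in 4.1 covers logistic and survival models at 7 and 14 days for the first visit window, and at 7 and 10 days for data collected at 40 weeks. It adds: "The same censorship criteria will be applied".

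**The concern.** The endpoint and the censoring criterion overlap. A spontaneous labour that starts after the 12-hour mark, with no induction before it, satisfies both. The 4.1 rule settles the conflict by censoring, so a real event is entered as a non-event.

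The date is a second matter. The group is defined by what has not happened after 12 hours, but the censoring is placed at an admission. If that admission came before the 12-hour wait, a woman's status at that moment is decided by later information. Kaplan-Meier and Cox estimates require that leaving the risk set does not depend on the future event. Here the non-labouring women would be taken out of the risk set for hours in which they were observed, and the labouring women would stay in it.

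At stake are the daily probability of onset (secondary objectives 2 and 5) and the fixed-window analyses that inherit the same criteria.

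**Working it through.** **Side by side.** Take three women admitted with ruptured membranes, with hour 0 at that admission and the 12 hours counted from it:

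| Woman | What happens | Main outcome (2) | 4.1, admission with rupture | 4.1, later admission after the wait |
|---|---|---|---|---|
| A | Labours at hour 6 | Event | Event at hour 6 | Event at hour 6 |
| B | No labour, induced after hour 12 | No event | Censored at hour 0 | Censored at or after hour 12 |
| C | Labours at hour 14, no induction before | Event at hour 14 | Censored at hour 0 | Meets the criterion; censored |

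Woman C is lost as an event in both columns, because of the 12-hour cut-off. Woman B is dated from future information only in the first column.

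**The plan's own figure.** The sample size section assumes "approximately 78% of women will start their labor spontaneously before 41 weeks" and plans by "considering 10 events (spontaneous onset of labor) for each of these 15 variables", doubled for two models:
- 10 / 0.78 = 12.8, rounded up to 13 women per variable
- 13 × 15 × 2 = 390
- 390 × 1.10 = 429

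The stated figures are reproduced. None of the inputs involves membrane rupture, so the sample size does not depend on this point.

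**Assumed inputs, none of them in the protocol:**
- prelabour rupture in 5–20% of women
- labour within 12 hours in 40–60% of those
- later spontaneous labour in 10–50% of the rest
- Weibull onset times, shape 1.6 and scale 10 days
- other censoring with mean 70 days, and follow-up ending at 17 days

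**Women affected.** The plain product is 429 × rupture share × (1 − share in labour by 12 hours):
- low: 429 × 0.05 × 0.40 = 8.6
- high: 429 × 0.20 × 0.60 = 51.5

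The simulation gives 6.9 and 41.6, about 81% of these, because some women are censored for other reasons or reach the end of follow-up before rupture. So about 7 to 42 women are censored by the rule. True events lost: 6.9 × 0.10 = 0.7 and 41.6 × 0.50 = 20.8, or about 1 to 21.

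**Effect on the Kaplan-Meier estimate.** Probability of onset by day 14, time in whole days, 300,000 simulated women per setting:

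| Rupture / labour by 12 h / later labour | Censor at admission with rupture | Censor at 12 h | Count later labours, else censor at induction |
|---|---|---|---|
| 5% / 60% / 10% | 0.811 | 0.811 | 0.811 |
| 10% / 40% / 30% | 0.795 | 0.794 | 0.799 |
| 10% / 60% / 50% | 0.803 | 0.802 | 0.809 |
| 20% / 40% / 10% | 0.772 | 0.769 | 0.773 |
| 20% / 40% / 50% | 0.772 | 0.769 | 0.791 |

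In the most extreme setting:
- back-dating alone: 0.772 − 0.769 = 0.003 upward
- lost events alone: 0.791 − 0.769 = 0.022 downward
- net effect of the back-dated rule: 0.791 − 0.772 = 0.019 downward

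At day 7 in the same setting the three values are 0.387, 0.385 and 0.403, a net difference of 0.016. Continuous time gives differences of the same size. The 10-day window and the Cox coefficients were not calculated.

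**The case against.** The strongest reply is that back-dating is inferred. The cause named in 4.1 is the whole phrase, rupture with no labour after the wait, so admission for that cause could be an admission once the wait has failed. Section 3.4 fits that reading. The protocol does not say where the 12 hours are spent or when they start. This stands: the second problem holds on one reading only. The protocol does not choose between the readings, though, and a rule that fixes follow-up time should not leave the choice open.

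It can also be said that ending follow-up a fixed time after rupture is a legitimate outcome definition, and that a labour after censoring is simply unobserved. That would be so if 2.2 limited the event to labours within 12 hours of rupture. It does not.

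A reader might infer three stronger claims that the documents do not support:
- *Back-dating causes the later labours to be lost.* The 12-hour cut-off loses them; censoring at exactly 12 hours would lose them too.
- *Everyone left in the risk set is an event by construction.* At most this is true of women with prelabour rupture after admission, on one reading, and leaving aside withdrawal or other censoring.
- *The main logistic outcome is misclassified as well.* Main outcome (1) contrasts spontaneous onset with induction for gestational age and carries no 12-hour condition. The link to binary analyses runs only through the secondary windows that take over the censoring criteria.

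Finally, the effect is small and the outcome is counted in days. This stands too.

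**Conclusion.** The point holds as a defect of definition with a small numerical effect. Recording later spontaneous labours as censored contradicts main outcome (2) under either reading of 'admission'. Dating the censoring from future information follows on the more direct reading and does not fit section 3.4.

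Under the assumed rates, about 1 to 21 of 429 women have a true event recorded as censored. The estimate moves by at most about 0.02 from this and by at most about 0.003 in the opposite direction from back-dating. The upper ends need rupture in 20% of women and spontaneous labour in half of those not in labour by 12 hours. With other rates the size would change; the overlap in definitions would not. How many women labour between hour 12 and induction depends on local guidelines that are not shown.

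The case for acting is that the definition would be wrong or read differently between sites, and that it is hard to repair later if the start of induction is not captured. It does not rest on a large bias. Whether induction should be handled as a competing event is a separate question.

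**What to change.** Reconcile sections 2.2, 3.4 and 4.1 on one data rule, for the survival analysis and for the 7-, 10- and 14-day analyses that use the same censoring criteria:
- spontaneous onset at any time before induction starts is an event, dated at its own time
- otherwise, follow-up is censored at the actual start of induction, not at an earlier admission

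Remove the undefined reference to admission from 4.1, and add the date and time of induction start to the eCRF. Section 7.2 already has perinatal results collected from clinical records, so this time can be sought from the same source. The rule works under either reading of the present text and changes only how data are classified; clinical management stays with local guidelines.

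The cost is a short text change in three sections and one extra eCRF field.
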